# Allogeneic human umbilical cord-derived mesenchymal stem cells for severe bronchopulmonary dysplasia in children: study protocol for a randomized controlled trial (MSC-BPD trial)

**DOI:** 10.1186/s13063-019-3935-x

**Published:** 2020-01-31

**Keywords:** Bronchopulmonary dysplasia, Human umbilical cord-derived mesenchymal stem cells, Clinical trial, Protocol

## Abstract

**Background:**

Bronchopulmonary dysplasia (BPD) is a complex lung pathological lesion secondary to multiple factors and one of the most common chronic lung diseases. It has a poor prognosis, especially in preterm infants. However, effective therapies for this disease are lacking. Stem-cell therapy is a promising way to improve lung injury and abnormal alveolarization, and the human umbilical cord (hUC) is a good source of mesenchymal stem cells (MSCs), which have demonstrated efficacy in other diseases. We hypothesized that intravenously administered allogeneic hUC-MSCs are safe and effective for severe BPD.

**Methods:**

The MSC-BPD trial is a randomized, single-center, open-label, dose-escalation, phase-II trial designed to investigate the safety and efficacy of hUC-MSCs in children with severe BPD. In this study, 72 patients will be enrolled and randomly divided into two intervention groups and one control group. Patients in the intervention groups will receive a low dose of hUC-MSCs (*n* = 24; 2.5 million cells/kg) or a high dose of hUC-MSCs (*n* = 24; 5 million cells/kg) in combination with traditional supportive treatments for BPD. The patients in the control group (*n* = 24) will be treated with traditional supportive treatments alone without hUC-MSCs. The primary outcome measures will be cumulative duration of oxygen therapy. Follow-up assessments will be performed at 1, 3, 6, 12, and 24 months post intervention, and the key outcome during follow-up will be changes on chest radiography. Statistical analyses will evaluate the efficacy of the hUC-MSC treatment.

**Discussion:**

This will be the first randomized controlled trial to evaluate the safety and efficacy of intravenously administered hUC-MSCs in children with severe BPD. Its results should provide a new evidence-based therapy for severe BPD.

**Trial registration:**

ClinicalTrials.gov, ID: NCT03601416. Registered on 26 July 2018.

## Background

Bronchopulmonary dysplasia (BPD) is a common chronic lung disease whose incidence is increasing annually, especially in this time of the two-child policy in China [1, 2]. Patients with BPD usually have ventilator or oxygen dependence during the early stage of the disease [3]. Most patients can gradually withdraw from the ventilator or stop oxygen treatment at different times depending on disease severity, but abnormalities in pulmonary structure and lung function may last until late childhood and even adulthood, especially in those who are diagnosed as severe BPD according to the diagnostic criteria of the National Institute of Child Health and Human Development (NICHD) [4, 5]. The mortality of overall BPD patients is about 15% [6]; nevertheless, the mortality rate of severe BPD reaches 41%, creating an enormous threat to the health of these children [4, 7]. More than 50% of survivors with BPD experience hospital readmission for repeated lower respiratory infections in the first year or two, which causes serious economic and labor burdens on families [4, 8]. Although surfactant treatment [9], prenatal steroid usage [1, 10], ventilator strategies [11], and improved nutrition [12] are used in BPD patients, effective therapies are lacking [13]. Therefore, identifying novel effective therapies for severe BPD in children is urgent and significant.

In recent years, the rapid development of stem-cell technology and regenerative medicine has identified stem cells as potential treatments for various refractory diseases, which are difficult to treat by traditional medical methods, such as degenerative diseases, cancer, and tissue damage [14–16]. Mesenchymal stem cells (MSCs) are a class of adult stem cells derived from the mesoderm with characteristics of non-tumorigenicity, low immunogenicity, and powerful paracrine function, and can be isolated from several sources, including bone marrow, human umbilical cord (UC), adipose tissue, amniotic fluid, and other tissues [17, 18]. Among them, human umbilical cord (hUC)-derived mesenchymal stem cells (hUC-MSCs) are useful in clinical application because they are easy to obtain, more proliferative, and have more powerful paracrine function than any other sources; they are effective at relieving lung inflammation, fibrosis, angiogenesis, and apoptosis [19–23]. Interestingly, the therapeutic potential of hUC-MSCs in several animal pulmonary disease models, including BPD, acute lung injury, and idiopathic pulmonary fibrosis, were confirmed [21, 24, 25]. Approximately 75% of hUC-MSCs reportedly accumulate in the microvessels of the lungs [26]. Hence, the therapeutic potential of hUC-MSCs for severe BPD in children requires investigation.

A multicenter, dose-escalation, phase-I clinical trial (NCT01775774) investigated the safety and efficacy of bone-marrow-derived MSCs for moderate to severe acute respiratory distress syndrome (ARDS) in adults without any adverse events (AEs) related to infusion reported, which had potential efficacy [27]. The study reported that hUC-MSC treatment was safe in patients with moderate to severe chronic obstructive pulmonary disease (COPD) (NCT00683722) [28]. Another phase-I trial reported treating nine BPD patients in Korea with hUC-blood-derived mesenchymal stem cells (hUCB-MSCs) (NCT01297205) [29]. The follow-up data from this study showed the safety of hUCB-MSC administration and the ability to reduce the level of profibrotic factors in tracheal aspirates [30]. Despite these data indicating the safety of MSC infusions for patients with pulmonary diseases, the limited sample size and lack of appropriate controls in those trials were insufficient to show the efficacy of MSC treatment. A large sample size of phase-II trials with matched controls is required to further investigate hUC-MSC safety and efficacy. Based on the previous promising findings, we designed an MSC-BPD trial to evaluate the safety and efficacy of the intravenous infusion of hUC-MSCs in children with severe BPD.

## Methods

### Study objectives

The goal of this clinical trial is to test the safety and efficacy of hUC-MSCs in children with severe BPD. There are three specific objectives:
Evaluate the long-term safety and efficacy of intravenously administered hUC-MSCs in children with severe BPDTest the hypothesis that the administration of hUC-MSCs can reduce the duration of mechanical ventilation and oxygen and improve impairment of the pulmonary structure in children with severe BPD; andExplore the potential therapeutic mechanism of hUC-MSCs for severe BPD

### Study design and setting

The MSC-BPD trial (registered at www.clinicaltrials.gov (no. NCT03601416) is a randomized, single-center, dose-escalation, phase-II trial aiming to evaluate the safety and efficacy of hUC-MSCs in a total of 72 children with severe BPD. A study flow chart of the trial is shown in Fig. 1. The study protocol will be reported based on Standard Protocol Items: Recommendations for Interventional Trials (SPIRIT) guidelines (Additional file 1).

**Fig. 1 Fig1:**
[figure not shown]
Study flow diagram

This trial will be conducted at the Children’s Hospital of Chongqing Medical University (CHCMU) in Chongqing, China.

### Sample size and calculation

The sample size of this phase-II randomized controlled trial was calculated by power analysis using the Power and Sample Size online calculator (http://powerandsamplesize.com/). The trial is designed to investigate the hypotheses of two interventions compared to control, but it is not powered to test differences between the two intervention groups. The larger of the two numbers is the sample size of this trial. The primary outcome measure is the change in the cumulative duration of oxygen therapy. The cumulative mean duration of severe BPD is reportedly 90 ± 15 days [4, 31]. This trial is powered to identify differences of 15% (from 90 days in the control group to 77 days in the low-dose groups) and 20% (from 90 days in the control group to 72 days in the high-dose groups) in participants who accept the hUC-MSC intervention. Meanwhile, the power is set at 0.8, type I error *ɑ* is 0.05, and type-II error *β* is 0.20. The calculated sample size is 21 for each group. To account for the possibility of 10% of patients being lost to follow-up, the final sample size will be 24 and the total size will be 72.

## Participants

### Patient and public involvement

The participants will not be involved in the development of the trial including the study design, recruitment, and conduct, selection of research question, and outcome measures. The participation will be voluntary and the participants will have freedom to participate or withdraw from this trial at any time throughout the study. The participants’ privacy will be protected.

Participants will be enrolled in this study according to the inclusion and exclusion criteria (Table 1). The parents or guardians of all participants will provide the written informed consent form approved by the Ethics Committee of Stem Cell Clinical Research of CHCMU.

**Table 1 Tab1:** Inclusion and exclusion criteria for participants with severe bronchopulmonary dysplasia (BPD)

Inclusion criteria	
1. Participants who are male or female and whose age is 0–1 years old 2. Participants who are diagnosed as severe BPD according to diagnostic criteria of BPD made by the National Institute of Child Health and Human Development (NICHD )[5]. 3. Participants who have abnormal respiratory manifestations and the Silverman-Anderson score [32] is more than 3 points 4. Written informed consent signed by a legal representative or a parent	
Exclusion criteria	
1. Participants whose age is more than 1 year old 2. Participants who have no signs of dyspnea or BPD-related changes in pulmonary imaging, such as central apnea or diaphragmatic paralysis although mechanical ventilation or oxygen are required 3. Participants who have concurrent cyanotic or acyanotic congenital heart diseases, except for patent ductus arteriosus, and atrial septal defect and ventricular septal defect with defect < 5 mm 4. Participants whose important laboratory test (liver and kidney functions tests, cardiac markers, hematology and immunity tests, urinalysis, etc.) abnormalities are more than three times compared with the normal value 5. Participants who have severe pulmonary hypertension confirmed by cardiac ultrasound at the time of assessment 6. Participants who have severe respiratory tract malformation, such as Pierre-Robin syndrome, tracheobronchomalacia, vascular ring syndrome, congenital tracheal stenosis, tracheo-esophageal fistula, pulmonary emphysema, pulmonary sequestration, congenital pulmonary dysplasia, congenital pulmonary cyst, congenital spasm, etc. 7. Participants who have severe chromosome anomalies (such as Edward syndrome, Patau syndrome, Down syndrome) or severe congenital malformation (such as hydrocephalus, encephalocele) or hereditary diseases 8. Participants who have severe congenital infection such as *Herpes simplex*, toxoplasmosis, rubella, syphilis, AIDS, etc. 9. Participants who have severe active infection when C-reactive protein (CRP) > 30 mg/dL, or suffer sepsis or septic shock 10. Participants who are going to have surgery within 72 h before/after this study hUC-MSCs administration 11. Participants who have surfactant administration within 24 h before this hUC-MSCs administration. 12. Participants who have severe intracranial hemorrhage ≥ grade 3 or active pneumorrhagia or active air-leak syndrome 13. Participants who are using hormones or needing hormones within and after 7 days of hUC-MSCs administration 14. Participants who are participating in other interventional clinical trials 15. Participants who are considered inappropriate by the investigators or whose parents cannot provide informed consent	

### Inclusion and exclusion criteria

The inclusion and exclusion criteria are listed in Table 1. Participants will be 0–1 year of age. The diagnostic criteria and BPD severity gradation refers to the criteria established by the NICHD workshop [5]. The Silverman and Andersen score is used to assess the severity of abnormal respiratory manifestations [32].

### Recruitment

Patients can only be enrolled in this study after passing the citywide consultation resolution and signing the informed consent form.

Participants will be recruited from three sources. First, the parents of potentially eligible hospitalized patients diagnosed with severe BPD will be approached and asked to join this study. Second, physicians will generate lists of patients from the electronic medical records of CHCMU with a diagnosis of BPD who were discharged within 1 year. Investigators or physicians will contact the patients’ parents by telephone or mail them a research leaflet and recruitment letter. Third, physicians will post study flyers at the outpatient department, the official website, and the WeChat public platform of CHCMU for those diagnosed with severe BPD at other hospitals. If the parents of these patients with severe BPD are interested in this research, we will initiate the screening process.

A multidisciplinary consultation will be held to confirm whether these potential participants meet the general diagnostic criteria of BPD as well as the inclusion and exclusion criteria. The consultation will consist of a neonatologist, a respiratory physician, a radiologist, a laboratory physician, a Department of Critical Care Medicine expert, stem-cell treatment center researchers, and medical department staff. If more than 80% of experts agree on the hUC-MSCs treatment, these patients will be viewed as potential participants. The researcher will then arrange a meeting to communicate with the legal representative or parents about the clinical trial research details and sign the written informed consent form.

The following details of the clinical trial will be fully explained to the patients’ guardians as follows: (1) study purpose; (2) research background; (3) number of participants and duration of their participation; (4) study procedures; (5) potential discomfort and risks of treatment; (6) expected benefits; (7) protection of confidentiality and privacy; and (8) their participation is voluntary. Each patient’s legal representative or parents will sign the informed consent form after all the items above are fully understood. After that, the patients’ baseline characteristics will be recorded by the clinicians (Table 2).

**Table 2 Tab2:** Timeline and items of evaluation during the trial

Items		Study period									
		Screening phase	Treatment phase				Follow-up phase				
		− 2 weeks	Baseline	24 hours	3 days	7 days	1 month	3 months	6 months	12 months	24 months
Therapy	hUC-MSCs	√	√								
	Traditional treatment	√	√	√	√	√					
Informed consent		√									
Inclusion and exclusion criteria		√	√								
Demographic information		√									
Personal history/past history/family history		√					√	√	√	√	√
Height/weight/head circumference		√	√			√	√	√	√	√	√
Vital signs^a^/physical examination		√	√	√	√	√			√	√	√
Hematology^b^/blood biochemistry^c^/urinalysis^e^		√	√	√							
Infectious disease-related examination^d^		√	√	√							
Blood oxygen saturation/blood gas analysis			√	√	√	√			√	√	√
Chromosome examination		√									
Brain MRI examination		√							√	√	√
EKG		√	√	√							
Echocardiogram		√									
Ventilator parameters/oxygen therapy			√	√	√	√	√	√	√	√	√
Adverse events evaluation			√	√	√	√	√	√	√	√	√
Chest high resolution CT			√						√	√	√
Pulmonary function test			√						√	√	√
Mortality/complications of prematurity^f^							√	√	√	√	√

Legend: *CK-MB* creatine kinase-MB*, CT*, computed tomography *EKG* electrocardiogram, *hUS-MSCs* human umbilical-cord mesenchymal stem cells

^a^The indicators of vital signs include temperature, blood pressure, heart rate, respiratory rate, transcutaneous oxygen saturation

^b^The condition of hematology of participants will be estimated by hematological tests which contains white blood cell count, platelet count, red blood cell count, hemoglobin, the percentage of lymphocytes, the percentage of neutrophil and C-reactive protein (CRP)

^c^The items of blood biochemistry include liver function, renal function, cardiac markers, the indicators of immunity, and the detailed items of each test are listed as follow. Liver function tests: albumin, bilirubin, alkaline phosphatase, alanine aminotransferase, aspartate aminotransferase, prothrombin time, activated partial thromboplastin time. Renal function tests: creatinine, blood urea nitrogen, creatinine clearance, glomerular filtration rate. Cardiac markers: hypersensitive troponin I, CK-MB mass, myoglobin

^d^Infectious disease-related examination include markers of hepatitis/syphilis/HIV/tuberculosis

^e^The content of urinalysis includes pH, protein, specific gravity, glucose and ketone bodies, white blood cells, occult blood or red blood cells, nitrite, color, and turbidity

^f^Complications of prematurity include growth retardation or retardation, hearing abnormalities, retinopathy, pulmonary hypertension, left ventricular hypertrophy

### Randomization and blinding

Participants will be randomized into three groups in a 1:1:1 ratio after collection of the baseline data. The allocation sequence will be generated and sent to the investigators by a statistician. Participants will not be blinded during the phase-II trial and the patients in the control group will not be given hUC-MSC treatment.

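### The protocol sends the allocation sequence to investigators who help recruit and can exclude infants, and does not say that upcoming assignments are withheld until enrolment

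*Protocol article*

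**What the plan says.** Protocol article, Randomization and blinding, gives the order and the route of allocation in two consecutive sentences: "Participants will be randomized into three groups in a 1:1:1 ratio after collection of the baseline data", and then "The allocation sequence will be generated and sent to the investigators by a statistician". The same section adds "Participants will not be blinded during the phase-II trial". The Abstract describes a "randomized, single-center, open-label, dose-escalation, phase-II trial".

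Three other places bear on who can influence entry:

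- Recruitment, on patients already discharged: "Investigators or physicians will contact the patients’ parents by telephone or mail them a research leaflet and recruitment letter".
- Table 1, exclusion 15, removes "Participants who are considered inappropriate by the investigators".
- Recruitment, on the multidisciplinary consultation: "If more than 80% of experts agree on the hUC-MSCs treatment, these patients will be viewed as potential participants". The panel includes researchers from the stem-cell treatment center.

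The article does not say when the investigators receive the sequence, or whether they receive it as a list or one assignment at a time.

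**The concern.** Concealment requires that whoever decides on an infant's entry cannot know the next assignment when deciding. The article describes a route for the sequence, and on its ordinary meaning that route ends with people who have a hand in entry. The problem is therefore what the text states, and not merely a detail left to the full protocol.

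An investigator who knows that the next slot is a control slot can delay an approach to a family, or judge an infant unsuitable, and do the opposite for a cell-therapy slot. Three features make this matter more here:

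- Randomization is the main protection in a trial without blinding.
- Under Outcome evaluation, the primary endpoint runs from the start of oxygen to its end. As worded, days before randomization count, so part of the outcome may be visible at enrolment.
- Under Statistical analysis, oxygen duration is compared by a t test with no covariates named.

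**Working it through.** **1. Reading the passages together.** The object sent is the sequence, and the recipients are the investigators. Investigators appear among those who contact parents, and they hold the discretion in exclusion 15. Randomizing after baseline data fixes when a child is assigned. It does not say that the investigators lack the upcoming assignments during screening and consent.

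**2. The plan's own figure.** Inputs from Sample size and calculation: control mean 90 days, SD 15, low-dose mean 77, high-dose mean 72, α 0.05, power 0.80. With the normal approximation, two-sided:

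n = 2 × [(1.960 + 0.842) × SD / difference]²

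- Low dose, difference 13: n = 20.9, so 21.
- High dose, difference 18: n = 10.9, so 11.

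The larger is 21, as stated. Allowing for 10% loss, 21 / 0.9 = 23.3, so 24 per arm and 3 × 24 = 72. The figures reproduce, and concealment does not alter them.

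**3. What a selection shift would do.** Assume no treatment effect and a difference b in expected oxygen days caused by selection alone. The standard error is 15 × √(2/n), and the rejection rate comes from the non-central t distribution with 2n − 2 degrees of freedom and non-centrality b / SE. For n = 21, SE = 4.63 and the critical value is 2.021. For n = 24, SE = 4.33 and the critical value is 2.013. The values of b are **assumptions**; the documents give none.

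| Assumed shift b (days) | Two-sided rejection, 21 per arm | 24 per arm |
|---|---|---|
| 0 | 5.0% | 5.0% |
| 3 | 9.7% | 10.4% |
| 5 | 18.4% | 20.4% |
| 8 | 39.2% | 44.0% |

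The smallest observed difference that reaches significance is 2.021 × 4.63 = 9.4 days with 21 per arm, or 2.013 × 4.33 = 8.7 days with 24.

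**4. How much steering those shifts would take.** Assume that the recruiter knows each slot and passes over an infant with the "wrong" visible prognosis (worse than average for a cell slot, better than average for a control slot) with probability p. Let r be the correlation between visible prognosis and oxygen duration. Both p and r are **assumed**. With normal prognosis, the expected bias is

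2 × 15 × r × 0.798 × p / (2 − p) = 23.94 × r × p / (2 − p),

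where 0.798 = √(2/π).

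- At r = 0.5, p of 0.25, 0.5 and 1 gives 1.7, 4.0 and 12.0 days.
- Simulation of the same model (24 per arm, 1,500 trials per setting, r = 0.5) gave 1.8, 4.0 and 12.0 days. False results favouring the cells occurred in 6%, 15% and 84% of trials per contrast, against a nominal 2.5%.
- Over r = 0.3 to 0.7, the simulated false-positive rate was 4% to 9% at p = 0.25, 8% to 25% at p = 0.5, and 39% to over 99% at p = 1.
- A bias of 13 days needs r × p / (2 − p) = 13 / 23.94 = 0.543. At r = 0.7 that means p of about 0.87. At r = 0.5 it is out of reach even with p = 1.

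**The case against.** The strongest defence is that the damaging reading is not spelled out. The sentence does not say that the complete list is sent, or that it is sent before enrolment. The sentence before it places randomization after baseline data, and Recruitment puts consultation, consent and baseline recording in that order. If each assignment is communicated only at that point, the panel vote and consent are already past. A condensed article may also leave the release mechanism to the full protocol, so the absence of envelopes or a central service is not an error in itself.

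This limits the point but does not answer it. The text names the sequence, not an assignment, as what is sent, and nothing withholds it during screening. If release is in fact one at a time, the sentence misdescribes the procedure and still needs correcting.

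Four further objections stand in part:

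- **Investigators do not control entry alone.** Eligibility also passes through a panel that needs more than 80% agreement, and nothing says that the panel sees the sequence. The telephone and mail contact is by investigators or physicians and concerns one of three recruitment sources. Exclusion 15 is the clearest point of personal discretion.
- **Lack of participant blinding is a different matter.** It concerns knowledge after assignment. It raises the stakes but is not evidence of failed concealment.
- **A reader might infer that the bias could be neither detected nor corrected.** That goes too far. Table 2 records oxygen and ventilator data, blood gases, chest CT and lung function at baseline, and Statistical analysis compares the groups at assignment. Measured imbalance can be partly seen and adjusted for; selection on unrecorded prognosis cannot.
- **A reader might infer that steering would produce the trial's result.** The documents do not support this. It is a possibility whose size depends wholly on assumed behaviour.

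**Conclusion.** The point holds as a defect in a stated procedure. Followed literally, the sentence leaves allocation unconcealed in an open-label, single-center trial, and the planned unadjusted comparison would carry any resulting bias into the primary result. Receipt of the entire list in advance is the plain reading, not an established fact.

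The size cannot be estimated from the documents. The rejection rates of about 10%, 18% and 39% rest on assumed shifts of 3, 5 and 8 days, an SD of 15 and 21 analysed per arm. Mild steering would do less, and a shift near the planned 13 days would need near-complete steering. The sentence should still be corrected as a matter of priority: bias introduced at entry can be only partly repaired later, and it would affect secondary and safety comparisons as well.

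**What to change.** Replace the sentence on sending the sequence with wording to this effect: the statistician, or another person with no part in recruitment, holds the sequence; investigators never see the list; each assignment is disclosed for one infant at a time, only after consent, confirmed eligibility and baseline data have been logged and enrolment is irrevocable. If assignments are already released this way, correct the sentence to say so.

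The cost is a change of wording and a small release step per infant. The sample size stays at 21, 24 and 72. Trial status gives the trial as not yet recruiting at submission; if infants have since been enrolled, the report should state how their assignments were released.
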